Participants of the CDCC Pilot Scheme will receive protocol-driven multi-disciplinary risk assessment and management in private PHC allowing for timely intervention to prevent complications of HT/DM. To ensure the quality of the provision of continuous and holistic primary care, Scheme FDs must be registered in the Primary Care Directory and use the PHC reference frameworks as the standard care protocol for PHC services. District Health Centres (DHC) and DHC Express throughout the territory will serve as case managers to support FDs and coordinate with healthcare service providers to deliver network allied health services, laboratory service and drug service. According to the diagnosis, FDs will recommend comprehensive health management plans, provide necessary medication treatment, and set health targets together with participants. To support participants in disease prevention and management, nurse-led clinic will provide education, health assessment, and counselling services; whereas allied health professionals (including optometrists, podiatrists, dietitians, and physiotherapists) will provide individualised intervention services for participants. Each Scheme participant will be entitled to co-payment for services received under the CDCC Pilot Scheme which include subsidised FD, allied health, drug, and laboratory investigation services.

In order to assure that the CDCC Pilot Scheme is delivered with the intended care and achieves the expected health benefits, we will evaluate its quality of care, acceptability, effectiveness and cost-effectiveness to inform future PHC planning and policy.

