## Aims and objectives

This study aims to evaluate the quality of care, acceptability, effectiveness and cost-effectiveness of the CDCC Pilot Scheme. The objectives of this study are to:

Measure the adherence to the standards of care criteria by healthcare providers participating in the Scheme;Evaluate participant acceptability by self-reported outcomes on enablement, experience and satisfaction level about the services of the Scheme;Evaluate the effectiveness of the Scheme in improving health outcomes among CDCC participants over 12 months; and.Determine the provider costs and cost-effectiveness for delivering the CDCC Pilot Scheme relative to its effectiveness on participants health outcomes.

We hypothesize that:

Healthcare providers participating in the Scheme would achieve over 70% adherence for the standards of care criteria;60% of participants will report an increase in patient enablement levels after 12 months;90% of participants will report patient satisfaction 12 months after enrolment;A greater proportion of participants in the CDCC Pilot Scheme would achieve targets for disease control outcomes after 12 months compared to the comparison group; and.The Scheme would be cost-effective based on an incremental cost-effectiveness ratio (ICER) lower than the willingness-to-pay threshold of 1 annual gross domestic product (GDP) per person.

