#### Evaluation of the effectiveness and cost-effectiveness

Anonymous data including demographics, diagnoses, prescriptions and laboratory tests (e.g. full lipid profile and renal function test) at baseline and 12 months for CDCC participants will be extracted from the eHealth database and DHC IT module, whereas those for non-CDCC participants will be collected via a telephone survey by an independent professional survey provider, and they will complete the screening blood test at a designated laboratory. With the exception of critical results that requires immediate medical attention, participants of the comparison group will be asked to follow up on any abnormal results on their own.

Costs of the CDCC Pilot Scheme composes the of implementation and operation costs by health service providers and the direct medical costs of participants. The total costs of implementing CDCC services will include all expenditure incurred from setting up the programme until 31 Dec 2024, while ongoing operational costs would be collected over a 1-year period from Dec 2023– Dec 2024 (Appendix C). Costs will be collected from each DHC/DHC Express, a representative sample of service providers and the Primary Healthcare Commission at 12 months using a costing questionnaire.

Direct medical costs refer to the ongoing costs on utilization of public and private healthcare services (including hospitalization, Accident & Emergency department, General Out-patient Clinics, and Specialist Out-patient Clinics) for both CDCC and non-CDCC participants, as well as the co-payment for the CDCC services among CDCC participants, within 12 months from enrolment. The information will be extracted anonymously from the Hospital Authority’s eHealth database and Clinical Management System, and collected from participants through telephone survey at 12 months (Appendix D). The cost of public healthcare service utilization will be estimated by multiplying the frequency of utilization with the unit cost published in the Gazette and Hospital Authority ordinance (Chap. 113) of charges for non-entitled persons for each public healthcare service.

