### Data analysis

The proportion of patients and/or service providers achieving the standards of care, participant experience, satisfaction and enablement, and the costs of the CDCC Pilot Scheme and the direct medical costs from the participants at 12 months will be described with descriptive statistics. Differences in the proportion of participants reaching the targeted disease control outcomes between CDCC and non-CDCC participants will be compared using chi-squared tests, and adjusted for confounding factors by logistic regression. Changes in clinical parameters from baseline to 12 months will be compared between CDCC and non-CDCC participants by paired t-tests. The total mean costs on each CDCC and non-CDCC participant will be compared using t-tests. The additional costs required for an additional participant in the CDCC Pilot Scheme to achieve target outcomes of disease control after 12 months will be reported as the ICER, calculated as the incremental cost incurred for each participant of the CDCC Pilot Scheme divided by the difference in the proportion of participants meeting targeted disease outcome. Cost-effectiveness of the Scheme would be determined by comparing the ICER to the willing-to-pay threshold of 1 GDP per year.

All statistical analyses will be performed using Stata (version 15.1). A p-value < 0.05 is considered statistically significant.

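### The Scheme-cost formula adds participants' co-payments to providers' costs of the same services, so the ICER counts the co-paid share twice if provider costs are recorded gross

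*Protocol article*

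**What the plan says.** All places are in the protocol article.

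- **Evaluation of the effectiveness and cost-effectiveness.** Scheme cost is a sum of two terms: "implementation and operation costs by health service providers and the direct medical costs of participants". The second term covers use of public and private services in both arms, "as well as the co-payment for the CDCC services among CDCC participants, within 12 months from enrolment".
- **Same section, on the provider term.** "Costs will be collected from each DHC/DHC Express, a representative sample of service providers and the Primary Healthcare Commission at 12 months". For running costs, "ongoing operational costs would be collected over a 1-year period from Dec 2023" to December 2024. The cost items are in Appendix C, which is not shown.
- **Background.** Participants are "entitled to co-payment for services received under the CDCC Pilot Scheme which include subsidised FD, allied health, drug, and laboratory investigation services".
- **Aims and objectives.** The fourth objective is to "Determine the provider costs and cost-effectiveness for delivering the CDCC Pilot Scheme relative to its effectiveness on participants health outcomes".
- **Data analysis.** The ICER is the "incremental cost incurred for each participant of the CDCC Pilot Scheme divided by the difference in the proportion of participants meeting targeted disease outcome". The components of its numerator are not listed.
- **Outcome measures.** The ICER is a primary outcome. So, separately, is the difference between arms in health service utilisation and direct medical costs.

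**The concern.** A co-payment is income to the provider for a service whose resources the provider has also paid for. If the provider reports the full cost of delivering a consultation, drug or laboratory test, and the participant's payment towards it is then added, the co-paid part of that service appears twice. Only CDCC participants make these payments, so the excess falls on one arm and passes in full into the incremental cost.

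The ICER is to be judged against a threshold of one annual GDP per person, and its denominator is a small difference in proportions, so a modest excess per participant becomes a large one per additional participant at target. A larger sample or adjustment for confounders does not remove it, and neither does aligning the calendar windows of the two cost terms, because the overlap lies in what is counted.

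**Working it through.** The article states no cost or ICER value, so there is no figure to reproduce. The check is an accounting identity followed by a sensitivity calculation.

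**Inputs**
- Difference in proportion at target, ΔP: 3% as planned; 1.18% and 5.40% are the two cited results (Sample size calculation).
- Co-payment per CDCC participant, k: not given. 100 currency units is used as a scale.
- Full provider cost per CDCC participant, G: not given. Indexed at 100.
- Difference between arms in all other direct medical costs, O: not given. Assumed −50, 0 or +50 on the same index.

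**Step 1: the identity**
- The full incremental cost, with each service counted once, is G + O.
- If providers report gross, the stated sum is G + k + O, which is too high by k.
- If providers report net of co-payment income, or only the government-funded share is recorded, the sum is (G − k) + k + O = G + O, which is correct.

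**Step 2: which basis the text suggests**
- Set-up cost is described as every outlay up to the end of 2024, running cost as operational cost, and the fourth objective speaks of provider costs. None of this is the language of cost net of income, and no offset is mentioned.
- In the same section, public services are valued once, at published charges for non-entitled persons, and no patient fee is said to be added.
- Gross is therefore the more natural reading, but the text does not state it.

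**Step 3: shift in the ICER if gross**

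Shift = k / ΔP, with k = 100:
- ΔP = 3%: 100 / 0.03 = 3,333
- ΔP = 1.18%: 100 / 0.0118 = 8,475
- ΔP = 5.40%: 100 / 0.054 = 1,852

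Under net or government-share recording the shift is 0 at every ΔP.

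**Step 4: relative overstatement of incremental cost if gross**

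Overstatement = k / (G + O), with G = 100 and k an assumed 10, 30 or 50:

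| O | k = 10 | k = 30 | k = 50 |
|---|---|---|---|
| −50 | 20% | 60% | 100% |
| 0 | 10% | 30% | 50% |
| +50 | 7% | 20% | 33% |

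The spread shows that the percentage depends on inputs the article does not give.

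**The case against.** The strongest reply is that nothing shown proves a double count. What providers report is fixed by the costing questionnaire in Appendix C. If that form records cost net of fees, or only what government funds, adding the co-payment is the right way to reach full cost. An article may leave such itemisation to its appendix. The Data analysis section also names the costs of the Scheme and the direct medical costs separately and does not list what enters the ICER numerator. This stands, and it makes the point conditional. It does not dispose of it: the article does not merely omit a detail, it states a sum of two terms that overlap on the natural reading and mentions no offset.

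Two further objections stand in part. The sentence on co-payment is sound as a definition of what participants spend, and that spending belongs in the separate primary comparison of direct medical costs; the problem arises only when the two terms are combined for the ICER. The word co-payment is also used loosely: the Abstract and Background read as if it were something the Scheme provides. In the costing section it sits among participants' own costs, which fits participants' payments better.

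A reader might go further and infer that government subsidy is counted twice as well, because both the Primary Healthcare Commission and the service providers report costs, so that service cost is nearly doubled. The documents do not support this. They do not say that subsidy payments are a cost item or that they are added to recipients' costs, and no passage shows that subsidy plus co-payment equals the resource cost of a private provider.

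**Conclusion.** The point holds as a conditional flaw in a stated cost rule. Followed as written, with provider costs gross, the rule counts the co-paid share of CDCC services twice in the CDCC arm only. With a positive effect it raises the ICER by the co-payment per participant divided by the difference in proportions. With provider costs net of fees, or limited to the government-funded share, the error is zero.

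It would be tempting to conclude that the ICER is biased against the Scheme by a known factor. The documents do not allow that: they give neither the recording basis nor any amount, and the figures above are illustrations resting on an assumed co-payment, an assumed cost index and the planned or cited differences in proportion.

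Correction is still warranted, because the ICER is a primary outcome and the basis for the cost-effectiveness hypothesis.

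**What to change.** Restate the Scheme-cost formula in the costing section so that each CDCC service enters the ICER numerator once, and name the perspective. Either basis will do:

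1. gross provider cost, with the co-payment and any subsidy transfer left out; or
2. the government-funded share plus the co-payment, without the provider's own cost of the same services.

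The co-payment should not simply be deleted without first settling the basis. If provider costs prove to be net or government-share only, deletion would understate CDCC cost and favour the Scheme. Keep the co-payment in the separate comparison of participants' direct medical costs under either basis.

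The cost is a minor rewording of the costing plan, and a check that the costing questionnaire distinguishes gross cost from fee and subsidy income. If it does not, that split would have to be obtained from providers. This is best done before the cost components are combined.

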### Outcome measures

#### Primary

The proportion of participants and service providers achieving each criterion of the evaluation framework.Participant enablement measured by the PEI at 3 and 12 months.Differences in the proportion of CDCC and non-CDCC participants achieving the targeted disease control outcome after 12 months (systolic/diastolic BP < 140/90mmHg for HT, reduced HbA1c for pre-DM, HbA1c < 7% for DM).Differences in health service utilization rate and direct medical costs of CDCC and non-CDCC participants within 12 months from enrolment.The ICER for achieving the targeted outcomes for disease control.

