### Subjects

To evaluate the quality of care, all operators of the DHC/DHC Express, and selected FDs and allied health professionals, will be asked to complete quality of care questionnaires. All participants who have enrolled into the CDCC Pilot Scheme between 1 Jan and 30 Jun 2024 will be included in the evaluation of the standards on process and outcome of care.

A convenient sample of 548 CDCC participants would be recruited from all 18 DHC/DHC Express between 1 Apr 2024 and 31 Aug 2024 to complete a survey on self-reported outcomes on participant acceptability and enablement. A conservative target of 140 participants for each diagnosis (i.e., normal, pre-DM, HT and DM) will be set to ensure different patients are equally represented.

The effectiveness and cost-effectiveness of the Scheme will be evaluated by comparing the differences in health outcomes and healthcare utilization rates among CDCC and non-CDCC participants at 12 months after enrolment. Records for CDCC participants enrolled between 1 Jan and 30 Apr 2024 who meet the inclusion criteria to participate in the CDCC Pilot Scheme will be included as the intervention group, while participants in the comparison group would be non-CDCC participants recruited in the community through collaboration with local networks and organizations. Participants ≥ 45 years, without a known diagnosis of HT and/or DM, and provide informed consent are eligible to join the study.

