### Sample size calculation

The sample size needed for evaluating participant acceptability is based on the proportion of participants who showed an increase in enablement, measured by the Patient Enablement Instrument (PEI), one year after enrolment into the CDCC Pilot Scheme. Previous studies showed that 55.6–72.2% of participants reported PEI score > 0 after entering structured programmes for DM and/or HT [10–12]. Assuming the proportion of CDCC participants with PEI score > 0 at 12 months to be 50%, 383 CDCC participants are required with 5% margin of error and significance level of 5%. To allow for about 30% attrition, the sample size required will be 548.

The sample size for evaluating the effectiveness and cost-effectiveness was determined based on the difference in the proportion of patients achieving the targeted outcome for disease control after 12 months between CDCC participants and the comparison group. Previous studies evaluating the 12-month effectiveness of the multi-disciplinary Risk Assessment and Management Program for DM or HT implemented in public primary care in Hong Kong found that the proportion of participants achieving treatment target (glycated hemoglobin [HbA1c] < 7.0% or systolic/diastolic blood pressure [BP] < 140/90mmHg) increased by 5.40% [13] or 1.18% [14], respectively after 12 months, compared to patients receiving usual care. Assuming a conservative 3% increase in the proportion of participants achieving treatment target after 12 months in the CDCC group, a total of 378 participants with pre-DM, HT and/or DM are required to detect difference at a power of 80% with a significance level of 5%/ According to the Hong Kong Population Health Survey 2020, the prevalence of undiagnosed HT and DM among individuals aged 45–84 was 15.4% and 4.6%, respectively [15]. Previous studies reported that the prevalence of pre-DM was 2.3–8.9% in Hong Kong [15, 16]. Taking a prevalence of approximately 20% in total for pre-DM, HT and/or DM, and accounting for an attrition of 30%, a total of 1,886 non CDCC participants will be required.

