#### Secondary

Participant experience and satisfaction of the CDCC services at 3 and 12 months.Differences in the changes in mean BP or HbA1c between CDCC and non-CDCC participants with HT, pre-DM and/or DM from baseline to 12 months.Costs for the implementation and operation of the CDCC Pilot Scheme in its pilot phase (1–2 years).

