The data of the CDCC Pilot Scheme are captured in multiple IT modules and managed by the Primary Healthcare Commission. Since a range of personnel from different service providers can input and access participant data through the IT modules, monitoring data quality is of utmost importance for a valid and reliable evaluation. To achieve this, we have worked closely with the Commission to align our understanding of the data fields and their definitions. Several issues observed to date have included (i) incomplete data entry such as laboratory records, missing attendances and treatment plans, (ii) missing diagnoses of participants who are lost to follow-up after the initial screening phase, and (iii) missing consultation records by FDs who encounter difficulties using the IT system. To overcome these challenges, through discussion with the Commission and service operators, (i) participants' diagnosis will be defined by the latest treatment plan, the latest laboratory record will be used for evaluating effectiveness. Staff at DHC/DHC Express will also (ii) follow up with the FDs on the missing diagnosis and (iii) provide guidance on the system interface to the FDs who are in need.

Maintaining close collaboration and communication with stakeholders is the key to implementing this evaluation study. We shall gather their feedback through regular meetings and address the concerns from different parties, including the expectation of the health policymakers, the progress of deliverables achievement by service operators, and the practical difficulties encountered by frontline staff. The goal of this evaluation study is to consolidate the issues that arose in practice and advise on feasible solutions upon discussion with relevant stakeholders, with the aim of enhancing the capacity of providers to offer quality care and raise participant satisfaction. Results from this evaluation would provide practical and specific recommendations to inform optimal delivery of the CDCC Pilot Scheme, while the processes used to develop this evaluation can be easily adapted for similar cross-sector screening and management programme in the community to improve the delivery of primary healthcare services.

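### DM and HT control is scored as a 12-month level with no baseline reference, and the ICER divides by the unadjusted difference, so baseline imbalance between two non-randomised cohorts passes into the headline results

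*Protocol article*

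**What the plan says.** All references are to the Protocol article.

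- **Outcome measures, Primary.** The cohorts are compared on the proportion reaching target after 12 months: "systolic/diastolic BP < 140/90mmHg for HT, reduced HbA1c for pre-DM, HbA1c < 7% for DM". The pre-DM criterion is a change. The DM and HT criteria are levels with no baseline condition.
- **Subjects.** Entry is limited to people without known disease: "Participants ≥ 45 years, without a known diagnosis of HT and/or DM, and provide informed consent are eligible to join the study". HT and DM cases are therefore newly detected. The comparison group consists of "non-CDCC participants recruited in the community through collaboration with local networks and organizations", so allocation is not random.
- **Data analysis.** Proportions are "compared using chi-squared tests, and adjusted for confounding factors by logistic regression". The confounders are not listed. The ICER is the incremental cost "divided by the difference in the proportion of participants meeting targeted disease outcome", with no mention of adjustment.
- **Outcome measures, Secondary.** "Differences in the changes in mean BP or HbA1c between CDCC and non-CDCC participants" from baseline to 12 months are compared, which implies that baseline values exist in both groups.
- **Sample size calculation.** The planning effect is 3 percentage points between the groups.

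**The concern.** With a level outcome, the chance of being at target at 12 months depends heavily on where a person started. Randomisation would balance starting values on average. Here one group joined a subsidised Scheme and the other came through community networks, so there is no reason to expect equal baseline HbA1c or BP.

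A DM case below 7% at screening who stays there counts as a success. An HT case with BP only slightly raised is likelier to be below 140/90 mmHg a year later than one with markedly raised BP. If the cohorts differ in such cases, the crude proportions differ with no Scheme effect at all.

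The planned regression can deal with this for the effectiveness test if baseline values are in the model. It does not reach the ICER, whose denominator is the simple difference. The planning effect is only 3 points, so a shift of one or two points would materially change the cost per additional participant at target, and that figure decides the cost-effectiveness hypothesis.

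**Working it through.** **Plan's own figures.** The 3-point planning effect is a stated assumption and serves here only as a yardstick. The 378 participants derived from it cannot be reproduced, because no comparison-group rate is given. That is a separate matter, and 378 is not used below.

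**Inputs from Sample size calculation.** Undiagnosed HT 15.4%, undiagnosed DM 4.6%, pre-DM 2.3% to 8.9%. Ignoring overlap, the DM share *w* of diagnosed participants is:

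- 4.6 / (15.4 + 4.6 + 2.3) = 4.6 / 22.3 = 20.6%
- 4.6 / (15.4 + 4.6 + 8.9) = 4.6 / 28.9 = 15.9%

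Against the article's rounded total of 20%, the share is 4.6 / 20 = 23%.

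**Assumed inputs (not in the article).** *s* = share of DM cases below 7% at baseline, differing between cohorts by Δs = 10 to 20 points; *a* = probability of staying below 7%; *c* = probability of newly getting below 7%. There is no treatment effect, and *w*, *a* and *c* are equal in both cohorts.

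**Formula.** At 12 months the DM proportion at target is p = s·a + (1 − s)·c. The false difference is Δs·(a − c) among DM cases and w·Δs·(a − c) in the pooled outcome.

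Example: s = 0.5 versus 0.6, a = 0.9, c = 0.3. Then p = 0.45 + 0.15 = 0.60 versus 0.54 + 0.12 = 0.66, a false 6 points among DM cases. Pooled, this is 6 × 0.159 = 0.95 to 6 × 0.206 = 1.24 points.

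| a, c | a − c | Pooled, w = 15.9%, Δs = 10 | Pooled, w = 20.6%, Δs = 20 | Δs for a false 3 points, DM only | Δs for a false 3 points, pooled, w = 23% |
|---|---|---|---|---|---|
| 1, 0 | 1.00 | 1.6 | 4.1 | 3.0 | 13 |
| 0.9, 0.3 | 0.60 | 1.0 | 2.5 | 5.0 | 22 |
| 0.85, 0.4 | 0.45 | 0.7 | 1.9 | 6.7 | 29 |
| 0.8, 0.5 | 0.30 | 0.5 | 1.2 | 10 | 43 |

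The first row is the extreme in which nobody crosses the threshold.

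**Effect on the ICER.** Hold the incremental cost fixed, take the true difference as 3 points, and use the second row unrounded (0.955 and 2.475).

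- Imbalance favouring the Scheme: the ICER is multiplied by 3 / 3.955 = 0.76 to 3 / 5.475 = 0.55.
- Imbalance against it: the ICER is multiplied by 3 / 2.045 = 1.47 to 3 / 0.525 = 5.7.

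**HT.** HT makes up 15.4 / 28.9 = 53% to 15.4 / 22.3 = 69% of diagnosed participants. Each point by which baseline BP alone shifts HT control between cohorts therefore moves the pooled outcome by 0.53 to 0.69 points. The article gives nothing from which to size that shift.

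**The case against.** The main objection is that the plan already adjusts by logistic regression, and baseline HbA1c and BP are obvious covariates. A journal article may leave the covariate list to an analysis plan. That stands: an unlisted covariate set is not in itself a fault. It does not cover the ICER, because that formula is written out here and uses the plain difference.

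Several stronger readings are tempting, and the document does not support them.

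- **That screen-detected DM is mostly below 7% at entry.** No diagnostic cut-off and no baseline distribution is given, so the share is unknown.
- **That the plan ignores baseline.** The pre-DM criterion needs the baseline value, and change in mean BP or HbA1c is a between-group secondary outcome.
- **That people already at target cannot show benefit, or are counted as gains in the ICER.** Comparison participants follow up most abnormal results themselves, so some may deteriorate, and preventing that is a benefit. Equal shares who start and stay at target cancel in a between-group difference. They may dilute an effect, but only imbalance biases it.
- **That the planning effect is on a different scale from the outcome.** The sample size rests on a between-group difference, "compared to patients receiving usual care. Assuming a conservative 3% increase in the proportion of participants achieving treatment target after 12 months", which matches the primary outcome.
- **That screening values will be carried forward as outcomes.** The Discussion says "diagnosis will be defined by the latest treatment plan, the latest laboratory record will be used for evaluating effectiveness", but does not say that the screening record may serve as the 12-month one.

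The size is also open to challenge. The 10 to 20 point imbalance is assumed, its direction is unknown, and a false 3 points in the pooled outcome needs an imbalance of about 13 to 43 points at a DM share of 23%.

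**Conclusion.** The point holds in a limited form. A level outcome for DM and HT, two non-randomised cohorts and a crude ICER denominator together let baseline differences in control pass into the chi-squared result and the ICER. The logistic model may protect the effectiveness estimate, but as written it does not protect the ICER.

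Under the assumed 10 to 20 point imbalance, and with DM at 16% to 21% of diagnosed participants, the false pooled difference is about 1.0 to 2.5 points with moderate movement across the threshold (a = 0.9, c = 0.3). The 1.6 to 4.1 points are the upper extreme and should not be read as the expected bias. With more movement (a = 0.8, c = 0.5) it is about 0.5 to 1.2 points. These figures also assume that the diagnoses are pooled, which the pooled sample size and single ICER denominator suggest but the article does not state. Among DM cases alone, an imbalance of 3 to 10 points would produce a false 3-point difference. The change is worth making because its cost is small next to what depends on the ICER.

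**What to change.** Keep the clinical targets unchanged and amend Data analysis as follows.

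1. Make the primary contrast the adjusted risk difference from the logistic model, with a confidence interval. Baseline HbA1c (DM, pre-DM) and baseline systolic and diastolic BP (HT) are required covariates within diagnosis, both sets where both diagnoses apply. Pre-DM belongs here too, because a higher starting value is more likely to be followed by a lower one. Keep the chi-squared test as a descriptive crude comparison.
2. Use that adjusted risk difference as the ICER denominator in place of the crude one.
3. As a descriptive supplement, report results by baseline at-target status: newly achieved among those above target, maintained among those already there.

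The ICER should not be restricted to newly achieved cases, since that would ignore prevented deterioration.

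**Cost.** Wording and a little more analysis; the secondary outcome implies that the baseline values are already to be collected in both groups. Intervals in the baseline-status subgroups will be wider. Adjustment will not remove unmeasured confounding, and it is only as good as baseline values that reach the two groups' datasets by different routes.

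### Any fall in HbA1c counts as target achieved in pre-DM, so about half could succeed with no true change, and one proportion and one ICER appear to mix this with fixed-level targets

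*Protocol article*

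**What the plan says.** Under Outcome measures, Primary, the protocol article defines the targeted outcome separately for each diagnosis: "systolic/diastolic BP < 140/90mmHg for HT", "reduced HbA1c for pre-DM" and "HbA1c < 7% for DM". The first and third are levels to be reached. The second is the direction of a before/after change, with no minimum size and no end level.

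The Sample size calculation makes a single count across diagnoses: "a total of 378 participants with pre-DM, HT and/or DM are required". The assumed 3-point effect is drawn from two earlier programme evaluations, whose targets were "glycated hemoglobin [HbA1c] < 7.0% or systolic/diastolic blood pressure [BP] < 140/90mmHg". Neither is a pre-DM target.

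Data analysis defines the ICER as incremental cost per CDCC participant over the between-group difference in the proportion meeting the target. It compares proportions by chi-squared test and confounder-adjusted logistic regression. The continuous measure is a secondary outcome only: "Differences in the changes in mean BP or HbA1c between CDCC and non-CDCC participants". Data analysis assigns paired t-tests to that between-group comparison of changes.

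**The concern.** Two kinds of success share one name. A participant with hypertension or diabetes succeeds by being below a control level at 12 months. A participant with pre-DM succeeds if the second HbA1c reading is lower than the first by any amount, which measurement variation alone will often produce. People labelled pre-DM on a raised screening value may also drift down by regression to the mean.

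If the diagnoses are pooled, the primary proportion and the cost per additional participant at target combine these unlike units. A reader of the ICER could not tell whether the Scheme bought blood pressure and glucose control or small downward movements in HbA1c. The planning assumption gives no help, because no source behind it used such a criterion.

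**Working it through.** **Inputs from the protocol article.** Planned effect 3 percentage points, 80% power, 5% significance, 378 participants (Sample size calculation). Prevalences in the same section: undiagnosed HT 15.4%, DM 4.6%, pre-DM 2.3–8.9%.

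**Assumptions.** The article gives no HbA1c SD, reporting precision or pre-DM range. I take the SD of the 12-month change as 0.15–0.40 points, and reporting either continuous or to 0.1 point.

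**The plan's own figure.** No control-group proportion is stated, so 378 cannot be reproduced directly. Read as a total (189 per arm, two-sided), no control rate gives 80% power for 3 points; the smallest requirement is 257 per arm, at a control rate of 0% or 97%. Read as 378 per arm, it fits only near a control rate of 0.7% or 96.3%. For an outcome with a 50% control rate, 50% v 53% needs 4,356 per arm, and power is about 8% at 189 per arm and 13% at 378 per arm. The pooled control rate need not be 50%, because pre-DM is only part of the count. These figures show only that a criterion met by about half the controls was not in view when 378 was set.

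**Chance success in pre-DM, no true change.**
- Continuous HbA1c: P(fall) = 0.50.
- Reported to 0.1 point: P(fall) = Φ(−0.05/SD), which is 0.37 at SD 0.15 and 0.45 at SD 0.40.
- Selected on a raised baseline: I simulated a population mean of 5.5 or 5.7, between-person SD 0.3 or 0.4, within-person SD 0.10–0.20, reporting to 0.1, and an assumed baseline range of 5.7–6.4. P(fall) ran from 0.41 to 0.60.

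**Pre-DM share of cases, ignoring overlap.** 2.3/(2.3 + 15.4 + 4.6) = 2.3/22.3 = 10%; 8.9/(8.9 + 15.4 + 4.6) = 8.9/28.9 = 31%.

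**Effect on the difference if only a subset responds.** Suppose true responders succeed and everyone else succeeds by chance at rate p0. The pre-DM difference is then multiplied by (1 − p0), about 0.40–0.59. Halving a 3-point pre-DM difference to 1.5, with HT and DM at 3:
- 10% share: 0.90 × 3 + 0.10 × 1.5 = 2.85; the ICER rises by 3/2.85 − 1 = 5%.
- 31% share: 0.69 × 3 + 0.31 × 1.5 = 2.54; the ICER rises by 3/2.54 − 1 = 18%.

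**Effect if everyone shifts.** With a uniform extra fall of 0.1 point in the CDCC group:
- SD 0.3: 50% v Φ(0.1/0.3) = 63%, a difference of 13 points.
- SD 0.4: 50% v Φ(0.1/0.4) = 60%, a difference of 10 points.
- Pre-DM contribution to the pooled difference at SD 0.3: 0.10 × 13 = 1.3 to 0.31 × 13 = 4.0 points.
- Pooled difference if HT and DM contribute 3: from 0.90 × 3 + 0.10 × 10 = 3.7 to 0.69 × 3 + 0.31 × 13 = 6.1 points, which lowers the ICER.

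**Information kept.** The efficiency of the sign relative to the mean of a normal change is 2/π = 0.64, a loss of 36%. For a 0.1-point difference, the continuous outcome needs 2(1.96 + 0.84)²·SD²/0.1², about 142 per group (SD 0.3) or 252 (SD 0.4). The any-fall outcome needs 226 or 398, about 1.6 times as many.

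**The case against.** A reader might infer that chance successes must dilute the pooled outcome and inflate the ICER. The documents do not support a direction. Chance successes occur in both groups and cancel on average in the difference. Under a uniform shift, a cut at zero gives a larger difference than a stricter one: at SD 0.3, a cut at a 0.3-point fall gives 15.9% v 25.2%, 9 points rather than 13. It also needs more participants, 290 per group against 226. Precision alone therefore does not single out the any-fall rule among binary rules, and the HT and DM targets are dichotomies too.

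A reader might also infer that most of the HbA1c information is discarded, or that more than half of pre-DM participants will succeed by chance. The first is wrong: about 64% is kept. The second depends on reporting precision and selection, which the article does not give, and the chance rate may fall below half. Regression to the mean is not peculiar to pre-DM either, since participants enter without known HT or DM and those labels also rest on screening values.

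Two further points stand in part. Pooling is implied, not stated, and a fuller plan may report by diagnosis. Mean HbA1c change is already a secondary outcome, so the continuous data are not ignored. But the analysis named for it, a paired t-test, compares two readings within the same people and does not compare independent groups.

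Finally, taking pre-DM out of the main ICER would change the question, because pre-DM is one of the Scheme's named conditions. I accept that and do not propose it.

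**Conclusion.** The concern holds in a limited form. The pre-DM criterion has no minimum change, sits beside fixed-level criteria in what reads as one primary proportion and one ICER denominator, and has no basis in the sources for the 3-point effect. With no true change, roughly 40–60% of pre-DM participants would meet it, under the assumed SDs, reporting precision and selection.

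The consequence is distortion of unknown direction. If a subset responds, the pooled difference falls from 3.0 to between 2.85 and 2.54 points in the worked case. Under a uniform 0.1-point shift at SD 0.3, pre-DM alone supplies 1.3–4.0 points, so a small HbA1c movement with no benefit in HT or DM could account for much or all of the planned effect. These sizes rest on a 10–31% pre-DM share with no overlap between diagnoses. The change is worth making because it is cheap and uses data already planned for collection.

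**What to change.** - For pre-DM, base the comparative analysis on 12-month HbA1c regressed on baseline HbA1c, group and the confounders planned for the logistic model. This replaces the between-group paired t-test, adjusts for baseline differences in a non-randomised comparison and avoids the loss from using only the sign.
- Report the proportion with any reduction in HbA1c descriptively.
- Report the target proportion and ICER separately for HT, DM and pre-DM, with each numerator restricted to the costs of the participants in its denominator. State how participants with more than one diagnosis are counted.
- If a pooled proportion and ICER are kept, say so explicitly, state that they combine different kinds of success, and present them beside the results by diagnosis. Keep pre-DM in the evaluation.

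No new data are needed, as HbA1c at baseline and 12 months is already required for the listed outcomes. The cost is a little more analysis and less precise estimates, because numbers per diagnosis are smaller.
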